#### Building infrastructure to support training and data monitoring processes and developing implementation protocols to evaluate adaptability (specific aim 3)

CircumVent leadership at the Nigeria Institute of Medical Research (NIMR) will lead this effort with guidance from the Implementation Committee. Proposed training and protocols will be developed based on the medical device training manuals from the manufacturer and adapted to the context of Nigeria. The Implementation Committee will apply needs assessment findings to the adaptation of existing protocols and refine existing materials. The Implementation Committee will also work with the NCDC to convene a cadre of trainers, whose sole purpose is to train health workers on the appropriate use of the CPAP/O_2_ helmets. These trainers will serve as coaches and provide support, knowledge exchange, and performance feedback to health workers using the CPAP/O_2_ helmets. Products from this phase will include training manuals, curricula, and standard operating procedures for the practice facilitation strategy and the use of the CPAP/O_2_ helmet kits.

#### Recruitment of implementation sites, health worker training, CPAP/O_2_ helmet distribution, pilot testing of practice facilitation strategy, and assessment of feasibility and acceptability (specific aim 4 a).

All eight COVID-19 treatment centers will be recruited for the proposed study.

*Training of health workers to use the CPAP/O*_*2*_*helmets for non-invasive ventilation in COVID-19 patients*. Health workers will be trained on the components of the CPAP/O_2_ helmets, including the treatment, operation and cleaning protocols. The initial training will occur over 2 days, followed by a 1-day step-down and booster training sessions every 4 months over 1 year. Day 1 will focus on familiarizing workers with the CPAP device settings, understand and interpret oximeter readings, and general device maintenance. Day 2 will focus on training about the patient circuit, the logic of the tubing, and how to interface and work with the oxygen helmet, especially fitting it comfortably and effectively. The healthcare workers will have the opportunity to practice acquired skills via role playing and modeling with feedback, as well as review of the training materials.

*Training evaluation*. A baseline assessment will be done to evaluate the knowledge of the physician on the management of ARDS using the CPAP/O_2_ helmet. After the 2 days training, a post-training assessment will be done to evaluate the uptake of knowledge provided. The percentage improvement in knowledge will be used to determine the degree of uptake.

*Distribution of devices*. The Steering Committee will coordinate the distribution of devices using the feedback received from the stakeholder engagement. This distribution will consist of the following steps: (1) purchasing and transporting the CPAP/O_2_ helmet kits to Nigeria; (2) working with NIMR and the Nigerian Ministry of Health for the clearance of the devices through customs, their secure storage in Nigeria, and developing the protocol for disbursing the CPAP/O_2_ helmets to the treatment sites; and (3) NIMR will disburse the kits to the treatment centers and monitor their use.

*Practice facilitation strategy*. A practice facilitation strategy will be tailored to the needs of the eight treatment centers. Key stakeholders in the healthcare system (physicians, respiratory therapists, ICU doctors and ICU nurses) will take part in user testing of the developed practice facilitation strategy. For this purpose, the health workers who are expected to implement the use of the CPAP/O_2_ helmet solution for non-invasive ventilation will respond to a series of questions to explore the aspects of the devices and their implementation that are difficult to understand and probe their comprehension of the nature of the challenges.

*Training of practice facilitators using a train-the-trainer model*. After recruitment of practice facilitators, a “kick off” learning session will review components of the CPAP/O2 helmet solution for non-invasive ventilation and its protocol, quality improvement methods, the study timeline, and evaluation plan with the practice facilitators. Following this session, the key investigators and a pulmonologist will conduct a 2-day [train-the-trainer] training with them, followed by 1-day booster session after 4 months during the project implementation. The training will cover three core competencies of practice facilitation: data use to drive improvement, interpersonal skills, and quality improvement [17]. The training will help the facilitators achieve competencies in practice facilitation techniques such as effective communication skills, problem solving, promoting teamwork, consensus building, and goal setting. The training will combine didactic sessions with case-based learning, with booster sessions. The facilitators will serve as coaches, provide support, knowledge exchange, and performance feedback to the treatment centers.

### Is the use of the CPAP/oxygen helmet associated with a greater risk of COVID-19 infection among healthcare workers? (specific aim 4 b)

Healthcare personnel are at increased risk of acquiring COVID-19 infection [18]. Studies of other respiratory pathogens have documented increased transmission risk associated with aerosol generating procedures (AGP), many of which can generate both large droplets and small particle aerosols. Non-invasive ventilation is considered an AGP, but it is postulated that helmet ventilation may be associated with less risk of transmission of respiratory pathogens via aerosolization given containment in the helmet and negligible air dispersion.

A case-control study design will be implemented. We will enroll clinical and environmental hospital staff who have exposure to SARS-CoV-2 via provision of direct patient care or environmental care at the eight CircumVent study sites. Consenting and eligible health care workers will complete baseline testing for SARS-CoV-2-specific antibodies and complete an exposure assessment form summarizing risk factors and potential COVID-19 exposures in the prior 1 month. All healthcare workers assessed at time 0 comprise the retrospective study cohort. Individuals who test negative for COVID-19 antibodies at time 0 will be invited to participate in the prospective study. They will be followed for up to 6 months during which they will complete monthly encounter forms to assess community and healthcare-related exposures and to document any PCR-confirmed diagnoses of SARS-CoV-2 infection. However, the study will be censored and exit interview and a second sample for SARS-CoV-2 antibodies will be obtained if and when COVID-19 vaccine becomes available at the designated COVID-19 treatment centers.

In the retrospective study, a case is defined by seropositivity to SARS-CoV-2-specific antibodies, and a control is defined by seronegativity to SARS-CoV-2-specific antibodies. In the prospective study, a case is defined by seropositivity to SARS-CoV-2-specific antibodies, or a clinical case of SARS-CoV-2 infection confirmed by PCR testing, and a control is defined by the absence of infection, either by SARS-CoV-2 PCR or SARS-CoV2 specific antibodies.

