#### Implementation Committee

The Implementation Committee is comprised of medical directors/representatives of five of the eight COVID-19 isolation and treatment centers in Nigeria. The committee oversees implementation of the project including (a) identifying practice capacity of all eight COVID-19 treatment centers, (b) establishing a manual of procedures and data collection processes, (c) finalizing plans for program evaluation, and (d) testing the feasibility and acceptability of using the CPAP/O_2_ helmet solutions for NIV in COVID-19 patients. The Implementation Committee has been meeting weekly since June 2020 and since January 2021, meeting monthly.

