#### Quantitative data analysis

Both the retrospective and nested prospective case-control studies will compare differences in exposures and risk factors observed between cases and controls using Chi-square or Fisher’s exact test. All tests will use 2-tailed probability, with *P* values < 0.05 considered statistically significant. Variables that are statistically significant will be included in forward logistic regression analysis to arrive at independent measures of association.

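### The retrospective part of Aim 4b sets one month of recent exposure against seropositivity of unknown date, so on its own it cannot support a claim about helmet risk

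*Protocol article*

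**What the plan says.** The specific aim 4 b section of the Protocol article describes two linked case-control studies of hospital staff at the eight sites.

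- **Retrospective study.** "All healthcare workers assessed at time 0 comprise the retrospective study cohort". At that visit workers are tested for antibodies and "complete an exposure assessment form summarizing risk factors and potential COVID-19 exposures in the prior 1 month". For outcome status, "a case is defined by seropositivity to SARS-CoV-2-specific antibodies, and a control is defined by seronegativity to SARS-CoV-2-specific antibodies". The definition includes no infection date, earlier negative test or limit on how old the infection may be.
- **Prospective study.** "Individuals who test negative for COVID-19 antibodies at time 0 will be invited to participate in the prospective study". Exposure is then recorded forward in time: "They will be followed for up to 6 months during which they will complete monthly encounter forms".

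The Quantitative data analysis section treats the two alike: "Both the retrospective and nested prospective case-control studies will compare differences in exposures and risk factors observed between cases and controls". It applies chi-square or Fisher's exact tests at a two-sided 0.05 level and carries significant variables into forward logistic regression. No stated step requires exposure to come before infection.

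**The concern.** Antibodies show that an infection happened, not when, and they become detectable only some time after it. The exposure form looks back one month. For a worker infected earlier than that, the form describes duty after the infection. For a worker infected early in the month, most of the recorded time also follows it.

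The section is headed by the question whether the helmet raises infection risk among staff, and the Abstract names that risk as the objection to non-invasive ventilation. A mistimed comparison tends to shrink a real association, so a null result could be read as reassurance. If past infection affects current duty, the association could also be distorted in either direction. Either result would carry the same significance tests as the sound prospective comparison.

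**Working it through.** The article gives no sample size, event count or infection timing for Aim 4b, so there is no figure of its own to reproduce. The check asks how much the mismatch could matter.

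**Inputs from the article.** Exposure window: 1 month. Case: any seropositive result at time 0. The only calendar markers are indirect. "The Implementation Committee has been meeting weekly since June 2020", the move to monthly meetings came in January 2021 (7 months later), and registration was in June 2021 (12 months later). These show that the project spans many months. They do not date infections, sampling or helmet use.

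**Assumptions, not in the article.** Infection times of seropositive staff are uniform from L to T months before the test. T is 6 to 12. L, the lag to detectable antibody, is 0 or 0.5 month. Antibodies stay detectable throughout. 30% of controls are exposed.

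**Step 1: share of cases infected before the window opens**, (T − 1)/(T − L).

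- L = 0: 5/6 = 83% for T = 6; 11/12 = 92% for T = 12.
- L = 0.5: 5/5.5 = 91% for T = 6; 11/11.5 = 96% for T = 12.

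The share infected inside the window, f, is the complement: 17% and 8% without lag, 9% and 4% with it. With a lag, people infected too recently to be seropositive are not cases, so they leave the denominator.

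**Step 2: most favourable timing.** If every case was infected inside the window (T = 1), the average share of the window falling after infection is (1 + L)/2. That is 50% for L = 0 and 75% for L = 0.5.

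**Step 3: effect on the odds ratio.** Control odds are 0.30/0.70 = 0.429. A true odds ratio of 2 gives case odds of 0.857, so exposure in correctly timed cases is p1 = 0.857/1.857 = 0.462. Let s be the persistence of exposure from the month of infection to the reported month. Observed exposure in cases is

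f × p1 + (1 − f) × [s × p1 + (1 − s) × 0.30].

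For f = 1/6 and s = 0: 0.167 × 0.462 + 0.833 × 0.30 = 0.327. The odds are 0.486, and 0.486/0.429 = 1.13. All results for a true odds ratio of 2:

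| T, L (months) | f | s = 0 | s = 0.5 | s = 1 |
|---|---|---|---|---|
| 6, 0 | 0.167 | 1.13 | 1.52 | 2.00 |
| 6, 0.5 | 0.091 | 1.07 | 1.48 | 2.00 |
| 12, 0 | 0.083 | 1.07 | 1.48 | 2.00 |
| 12, 0.5 | 0.043 | 1.03 | 1.46 | 2.00 |

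The model is simple. It treats every infection inside the window as correctly timed, which Step 2 shows is generous. It also ignores newly infected, still seronegative workers who would be counted as controls.

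**The case against.** The strongest reply is that the damage depends on facts the article does not give, and that the design already contains its own remedy. Much of this stands.

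- **Persistence of duty.** Staff are enrolled because of direct patient care or environmental care, and such roles tend to last. Under full persistence the dilution disappears. This is a fair limit on the size, and for stable traits such as job role the last month may be a reasonable stand-in. It helps less for helmet contact, which is new at these sites: no persistence of duty can link a helmet to an infection that came before it.
- **Timing.** A reader might infer that most recorded exposures follow infection, or that many infections predate any helmet. The documents do not establish either. Seronegative controls have no infection to precede, so the first statement can concern cases only. Both depend on the dates of time 0, the infections and deployment. The project timeline is in a figure that is not shown.
- **Reverse causation.** A reader might infer that past infection changed recent duty, for example through reassignment or sick leave. That is possible, but nothing in the article documents it.
- **The form itself is not shown.** It may record earlier illness or test dates, and the one-month limit may not cover every risk factor. Absence of those items cannot be claimed. The stated window for exposures would still not match an undated case definition.
- **The prospective study is unaffected.** It starts from staff seronegative at time 0, and its monthly forms cover the interval in which new infections occur. Aim 4b therefore does not fall with the retrospective arm.

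What remains is a conflict between two stated rules, the exposure window and the case definition. Later analysis cannot recover exposure in months the form did not ask about.

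**Conclusion.** The point holds for cases in the retrospective study. Where infection came before the reported month, or early in it, the recorded exposure follows the outcome, and the planned comparison cannot by itself support a claim about helmet risk.

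The size is conditional. With infections even over 6 to 12 months and no antibody lag, about 83% to 92% of cases were infected before the window. A true odds ratio of 2 with 30% exposed would appear as about 1.03 to 1.13 under independent duty, about 1.5 under half-persistent duty, and nearly undiluted under stable duty. The lowest figures should not be quoted alone, because they need duty in one month to be unrelated to duty in the next.

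This should be fixed, but it does not undermine Aim 4b as a whole, since the prospective arm is not affected.

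**What to change.** State in the specific aim 4 b and Quantitative data analysis sections that the helmet-risk question is answered by the prospective cohort seronegative at time 0. Report the time-0 comparison as a descriptive or exploratory serosurvey with no causal claim about helmets. This is a change of wording only. Its price is that the retrospective arm loses its claim on helmet risk.

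If a retrospective contrast is kept:

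1. Extend the form to exposure by month since the site's first helmet use.
2. Record dates of any earlier PCR-positive test or COVID-19 illness, if the form does not already do so.
3. Apply any restriction on early infections equally to exposed and unexposed workers, for example by excluding all workers with known infection before the site's first helmet use.

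The restriction should not be tied to a worker's own first helmet exposure. Never-exposed cases have no such date, so the rule could remove only exposed cases. With no true effect, 100 cases and 30% exposed, cases split 30:70, as do controls. Dropping half of the exposed cases leaves 15:70, and (15/70)/(30/70) = 0.50, a false sign of protection.

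The cost of this option is a longer form and less exact recall over more months, possibly differing between cases and controls. Infections that were never tested or noticed would stay undated.

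### Seronegativity at time 0 alone makes a worker a retrospective control and admits them to the prospective study, so a documented earlier PCR-confirmed infection with no detectable antibody is analysed as uninfected in both parts

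*Protocol article*

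**What the plan says.** All the relevant rules stand in the protocol article's section on specific aim 4 b.

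- Retrospective case: "In the retrospective study, a case is defined by seropositivity to SARS-CoV-2-specific antibodies".
- Retrospective control: "a control is defined by seronegativity to SARS-CoV-2-specific antibodies".
- Entry to the prospective study: "Individuals who test negative for COVID-19 antibodies at time 0 will be invited to participate in the prospective study".
- Prospective case: "a case is defined by seropositivity to SARS-CoV-2-specific antibodies, or a clinical case of SARS-CoV-2 infection confirmed by PCR testing".
- Prospective control: "a control is defined by the absence of infection, either by SARS-CoV-2 PCR or SARS-CoV2 specific antibodies".

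At time 0, workers give a blood sample and "complete an exposure assessment form summarizing risk factors and potential COVID-19 exposures in the prior 1 month". A history of PCR-confirmed infection is not named among the baseline items. PCR appears in the data collection only on the monthly forms during follow-up of up to 6 months, which serve among other things "to document any PCR-confirmed diagnoses of SARS-CoV-2 infection".

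**The concern.** Within one section, PCR confirmation counts as infection after time 0 and plays no part before it. Take a worker with a documented positive PCR before time 0 whose antibody is undetectable at time 0. The stated rules make that worker a control in the retrospective comparison and then a candidate for the prospective study as someone not yet infected. One rule produces both errors, so treating the retrospective part as descriptive would not remove the second.

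Aim 4b is the study's safety question for staff. Infected workers among the retrospective controls pull associations towards the null if the misclassification does not depend on exposure. The Data analysis section carries only variables with P < 0.05 into the forward logistic regression, so a weakened association could also be dropped before adjustment. In the prospective part, workers with a past infection may not be at the same risk as the others they are compared with.

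**Working it through.** **Figures in the document.** The article states no sample size, prevalence, effect size or rate of antibody loss for aim 4b, so there is no figure to reproduce. The rules can be compared directly. The size can only be illustrated.

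**Applying the rules** to a worker with a positive PCR before time 0 and a negative antibody test at time 0:

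| Rule | Criterion stated | Result |
|---|---|---|
| Retrospective case | seropositive | not a case |
| Retrospective control | seronegative | control |
| Prospective entry | antibody negative at time 0 | invited |
| Infection during follow-up | antibody or PCR | the same kind of PCR result would count |

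**Retrospective illustration.** Every input is an assumption: true odds ratio (OR) 2; half the workers exposed; prior infection in the unexposed p0 = 10-40%; share of infected workers seronegative f = 5-30%; share of those with a documented PCR k = 20-50%; f and k the same in exposed and unexposed.

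- Prior infection in the exposed: p1 = 2·o/(1 + 2·o), with o = p0/(1 − p0).
- Observed OR under the stated rule: odds of p1(1 − f) divided by odds of p0(1 − f).
- After excluding PCR-known workers, the controls in group i are 1 − pi + pi·f(1 − k) and the cases stay at pi(1 − f).
- With average prior infection p, the infected share of controls is pf/(pf + 1 − p). The PCR-known share is k times that.

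Severe end (p0 = 0.4, f = 0.3): p1 = 0.571.

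- Stated rule: (0.400/0.600)/(0.280/0.720) = 1.71.
- Exclusion with k = 0.2: (0.400/0.566)/(0.280/0.696) = 1.76.
- Exclusion with k = 0.5: (0.400/0.514)/(0.280/0.660) = 1.83.
- Share of controls: p = 0.486, so 0.146/0.660 = 22% were infected. The PCR-known share is 4.4% (k = 0.2) to 11% (k = 0.5).

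| p0 | f | OR, stated rule | OR after exclusion (k = 0.2; 0.5) | Controls previously infected | Of which PCR-known (share of controls) |
|---|---|---|---|---|---|
| 10% | 5% | 1.99 | 1.99; 1.99 | 0.8% | 0.2-0.4% |
| 20% | 10% | 1.95 | 1.96; 1.98 | 3.5% | 0.7-1.8% |
| 40% | 30% | 1.71 | 1.76; 1.83 | 22% | 4.4-11% |

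**Exclude or recode as cases?** If k is the same in both exposure groups, the two give the same OR. Recoding multiplies the cases in both groups by the same factor, and the controls are identical. They differ when PCR testing depends on exposure. Assume no true effect (OR 1.0), 30% infected in both groups, 20% of those seronegative, and a PCR on record for 60% of exposed but 20% of unexposed seronegative infected workers.

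- Recoded as cases: (0.276/0.724)/(0.252/0.748) = 1.13.
- Excluded: (0.240/0.724)/(0.240/0.748) = 1.03.

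**Prospective part.** Assume no helmet effect, a 15% risk of infection in follow-up, and an 80% lower risk after past infection. With past infection in 10% or 20% of helmet staff and 5% of others, the risks are 0.138 or 0.126 against 0.144, and the ORs are 0.95 or 0.86. With the two groups' shares exchanged, the ORs are the reciprocals, 1.05 or 1.17. The sign depends entirely on which group has more past infection.

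**The case against.** The strongest reply is that each definition follows its data source. The retrospective part is one blood sample, read the same way in everyone. The prospective part has monthly forms that can pick up PCR diagnoses between samples. Uniform serology avoids dependence on who happened to be PCR-tested, and bedside staff may have been tested more than environmental staff. This stands as a reason not to redefine retrospective cases, and the 1.13 above shows the risk. Recoding also creates a timing problem: the baseline form covers the prior 1 month, while an infection whose antibody has waned is probably older. Neither argument supports keeping a known infection among the controls or among those at risk.

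A second reply is that the condensed article may leave the exclusion to the full protocol. Enrolment is limited to eligible workers without the criteria being listed, and the prospective control definition names PCR with no time window. That is possible. But the case, control and entry rules are written out and carry no such condition. If the control definition were read as reaching back before time 0, the matching case definition would turn an old infection into a prospective case, and the entry rule would still need correcting.

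A reader might infer something stronger: that up to about a fifth of the controls are known cases. The 22% at the severe end counts every seronegative past infection, many of which may never have had a PCR. The PCR-known part is at most 11% under the same assumptions. A reader might also infer that helmets will look falsely protective in the prospective part. That needs past infection to be commoner among helmet staff, and strong protection in people without detectable antibody. The documents support neither.

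**Conclusion.** The point holds in a limited form. As written, a documented earlier infection with no detectable antibody is treated as no infection in both parts of aim 4b, although PCR confirmation counts as infection during follow-up. Under the assumed ranges and non-differential misclassification, the part that can be corrected is negligible when prior infection is uncommon and antibody loss is rare. It is modest at the severe end. Even there most of the dilution remains, because infections never confirmed by PCR cannot be identified. Prospective bias is possible if past infection differs by helmet use, but its direction and size cannot be determined from the document. This is a cheap improvement to the design, not a flaw that invalidates the aim.

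**What to change.** Add one item to the existing time-0 form: any earlier positive SARS-CoV-2 PCR, with its date. Add one sentence to the definitions: seronegative workers with an earlier positive PCR are excluded from the retrospective controls and from the prospective at-risk group. Keep the serological case definition for the main retrospective analysis, and count these workers as cases only in a sensitivity analysis. State that PCR in the prospective definitions refers to tests after time 0.

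The cost is one form item, one sentence and the loss of a few participants. Undocumented infections stay misclassified, and a small bias (1.03 in the illustration) can remain if PCR testing differs by exposure. The item should be collected at time 0, because the history is harder to recover later.

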### Study aims

1: Convene a Steering Committee of key stakeholders and recruit implementation sites to provide oversight for the development of processes for communication, decision-making, coordination, and distribution of CPAP/O_2_ helmet solutions for non-invasive ventilation at the eight COVID-19 treatment and isolation centers.

2: Use the integrated Promoting Action on Research Implementation in Health Services (i-PARiHS) framework to guide needs assessment, perform stakeholder analysis of the treatment centers’ capacity to use high-flow oxygen therapy to treat COVID-19 patients, and use the findings to develop a context-specific, practice facilitation strategy to implement the CPAP/O_2_ helmet solution for non-invasive ventilation.

3: Build infrastructure to support training and data monitoring processes and develop implementation protocols to evaluate the adaptability of the strategy for implementing use of CPAP/O_2_ helmets for non-invasive ventilation.

4: (a) Train healthcare workers; distribute a CPAP/O_2_ helmet solution for non-invasive ventilation, pilot test the practice facilitation [implementation] strategy, and assess feasibility of its use and acceptability; (b) estimate the altered risk of SARS-CoV-2 infection among healthcare workers associated with the use of CPAP/O_2_ helmets for non-invasive ventilation.

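### In the prospective healthcare-worker study a PCR diagnosis alone makes a case, but neither PCR nor exit serology is fixed for everyone, so any difference in testing by helmet contact would bias the helmet odds ratio.

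*Protocol article*

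**What the plan says.** All of this is in the protocol article, mostly in the section on specific aim 4 b.

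- **Aim** (Study aims, 4 b): to "estimate the altered risk of SARS-CoV-2 infection among healthcare workers associated with the use of CPAP/O_2_ helmets for non-invasive ventilation".
- **Follow-up** of workers who are seronegative at time 0: "They will be followed for up to 6 months during which they will complete monthly encounter forms". One purpose of the forms is "to document any PCR-confirmed diagnoses of SARS-CoV-2 infection". No PCR schedule and no common trigger for testing is given.
- **Second antibody sample:** the section says that "a second sample for SARS-CoV-2 antibodies will be obtained if and when COVID-19 vaccine becomes available at the designated COVID-19 treatment centers". No sample at 6 months is described for workers who reach that point without vaccine arriving.
- **Prospective case:** "a case is defined by seropositivity to SARS-CoV-2-specific antibodies, or a clinical case of SARS-CoV-2 infection confirmed by PCR testing".
- **Prospective control:** "a control is defined by the absence of infection, either by SARS-CoV-2 PCR or SARS-CoV2 specific antibodies".
- **Retrospective study, for comparison:** "In the retrospective study, a case is defined by seropositivity to SARS-CoV-2-specific antibodies", so serology alone decides.

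The Quantitative data analysis section plans Chi-square or Fisher's exact tests, followed by forward logistic regression on the significant variables. It names no term for how often a worker was tested.

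**The concern.** Serology is a study procedure and can be applied alike to everyone. PCR, as described, is only written down when a diagnosis happens to have been made. Because the two routes are joined by an or, the chance that an infected worker is counted as a case depends on whether that worker had a PCR test.

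The control definition can have the same weakness in reverse. If there is no exit sample, a worker who was never PCR-tested has no evidence of infection and falls into the control group.

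The factor under study could plausibly be related to testing. Enrolment mixes clinical and environmental staff, whose reasons for being tested may differ, and the section notes that "Non-invasive ventilation is considered an AGP". If testing does differ by helmet contact, part of the helmet odds ratio reflects how hard infection was looked for, not how often it occurred. Adjusting for exposures in the logistic model does not remove this, because the error lies in the outcome.

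**Working it through.** The article gives no infection rate, testing rate, assay sensitivity or sample size, so there is no planned figure to reproduce. Every input below is an assumption, chosen to show how the size of the bias depends on exit serology.

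**Inputs (assumed).** True infection risk *r* = 0.10 in both groups, so the true odds ratio is 1. Share of infected workers who are PCR-tested *q* = 0.80 with helmet contact and 0.40 without. Every PCR test in an infected worker is positive. An exit sample detects *s* = 0.85 of infections. The two routes are independent.

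**Formula.** Share of infections detected when an exit sample is taken: D = 1 − (1 − s)(1 − q). Without an exit sample: D = q. Apparent case risk: p = r × D. Apparent odds ratio: [p1/(1 − p1)] / [p0/(1 − p0)].

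**Exit sample in everyone.**
- Helmet contact: D = 1 − 0.15 × 0.20 = 0.97, p = 0.097.
- Other staff: D = 1 − 0.15 × 0.60 = 0.91, p = 0.091.
- Odds ratio: (0.097/0.903)/(0.091/0.909) = 1.07.

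**Exit sample in half of each group.**
- Helmet contact: D = (0.97 + 0.80)/2 = 0.885, p = 0.0885.
- Other staff: D = (0.91 + 0.40)/2 = 0.655, p = 0.0655.
- Odds ratio: (0.0885/0.9115)/(0.0655/0.9345) = 1.39.

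**PCR only.**
- p = 0.080 versus 0.040.
- Odds ratio: (0.08/0.92)/(0.04/0.96) = 2.09.

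**Opposite direction.** If the less-tested group is the one with helmet contact, the odds ratios are the reciprocals: 1/1.07 = 0.93, 1/1.39 = 0.72 and 1/2.09 = 0.48.

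**Check with other inputs.** Take r = 0.20, PCR sensitivity 0.80, serology sensitivity 0.85 and PCR uptake 60% versus 30%.

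| Share with exit sample | Case risk, helmet vs other | Apparent odds ratio |
|---|---|---|
| 0% | 9.6% vs 4.8% | 2.11 |
| 25% | 11.8% vs 8.0% | 1.53 |
| 50% | 14.0% vs 11.3% | 1.29 |
| 75% | 16.2% vs 14.5% | 1.14 |
| 100% | 18.4% vs 17.7% | 1.05 |

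With uptake of 80% versus 20% and no exit sample, the odds ratio is 4.44. With everyone sampled and 80% to 90% of infections detected by serology, it lies between 1.03 and 1.14 over the two uptake contrasts.

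**Chance of a false finding.** With an assumed 200 workers per group, r = 0.20 and no exit serology, a two-sided test at 0.05 rejects in about 46% (60/30) or 95% (80/20) of studies although there is no true difference. With everyone sampled and 80% to 90% detection, it rejects in about 5% to 8%.

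**Same test in everyone.** If case status rests on the exit antibody result alone, p = r × s = 0.10 × 0.85 = 0.085 in both groups and the odds ratio is 1.00, whatever the PCR frequency.

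**The case against.** The strongest reply is that the causal premise is not in the document. A reader might infer that helmet staff are worried and therefore tested more, so that the bias must show as excess helmet risk. The text does not support that. The concerns mentioned in the abstract are about non-invasive ventilation and are not attributed to workers. The aim 4 b section goes on to postulate less transmission with a helmet, and the Background and treatment-protocol sections present the helmet as protective. Staff who believe this could seek testing less, which would reverse the bias. This part of the reply stands: the direction is unknown.

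Second, the article may simply omit PCR triggers that the full protocol sets out. That is possible. It would not change the case definition, which the article does fix.

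Third, admitting only seronegative workers and then defining a case by seropositivity presupposes follow-up serology. With a sample in everyone the bias is small, and 1.07 may even be high. If infections missed by serology are PCR-tested half as often (40% versus 20%), D is 0.85 + 0.15 × 0.40 = 0.91 versus 0.85 + 0.15 × 0.20 = 0.88, and the odds ratio is about 1.04. This also stands, but universal exit sampling is not stated, so the larger figures cannot be dismissed.

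Fourth, the control definition can be read as no evidence of infection by either method, so an untested worker with exit serology is still properly classified. The wording is ambiguous. The default-control problem bites only where the exit sample is missing.

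Finally, the word clinical may limit the PCR route to symptomatic illness, where testing may differ less. That narrows the problem without removing it.

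**Conclusion.** The point holds in conditional form. As written, the prospective outcome need not be ascertained in the same way in all workers: PCR alone can make a case, PCR is not scheduled, and exit serology is described only for the event that vaccine arrives. If testing differs by helmet contact, the aim 4 b odds ratio is biased and the planned regression does not repair it.

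The size turns mainly on exit serology. At a true odds ratio of 1 and the assumed 80% versus 40% testing, the apparent value is about 1.07 with everyone sampled, 1.39 with half sampled and 2.09 with PCR only, or the reciprocals if testing runs the other way. It would go too far to say that the plan inflates helmet risk or that no exit serology is intended. The article states neither, and the testing rates are assumptions.

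**What to change.** 1. Take the already planned second antibody sample from every prospective participant at exit, whether exit is at 6 months or at vaccine censoring.
2. Count no one as a control without that result.
3. Report the helmet association by seroconversion alone alongside seroconversion or PCR, so that the contribution of PCR-only cases is visible.
4. Record all PCR tests on the monthly form, including negative results and the reason for testing, and show testing frequency by helmet exposure.

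The cost is an exit sample from each worker, using an assay the study already plans, and one added form item. There are two downsides. Workers without an exit sample leave the control group, which loses some information and may introduce selection, so their number should be shown by helmet exposure. The seroconversion-only analysis also omits PCR-positive workers who have not yet seroconverted, which matters if vaccine censoring makes exit abrupt. Those workers remain in the combined analysis.
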